## Abstract

**Background:**

Despite the availability of vaccines, immunocompromised patients are still at high risk for severe COVID-19. Vaccination has been proven to be an effective measure in preventing severe SARS-CoV-2 infections; however, data on B- and T-cell responses are lacking. While vaccination schedules for the general population have been defined, achieving immunogenicity in patients who are immunocompromised remains a challenge.

**Objective:**

The primary objective is to analyze anti-spike–immunoglobulin G (IgG) titers after repeated messenger ribonucleic acid vaccinations in patients who are immunocompromised. Further objectives are to analyze data on humoral immune responses and to evaluate data on cellular immune responses.

**Methods:**

This multicenter, prospective, noninterventional study aims to determine the immunogenicity and reactogenicity of an implemented standard-of-care COVID-19 vaccination strategy in patients who are immunocompromised. A total of 100 patients will be recruited at three study sites. Patients are eligible for study inclusion when they are 18 years or older, vaccinated according to the recent version of the COVID-19 vaccination standard, and if the patient is immunocompromised according to stage 3 of the classification “Stages of Immunosuppression.” The study analyzes B- and T-cell responses generated within the standard-of-care COVID-19 vaccination strategy. Additional blood samples will be drawn at each scheduled outpatient visit. Study-related blood samples will be used to extract ethylenediaminetetraacetic acid plasma and peripheral blood mononuclear cells for evaluation of B- and T-cell responses to COVID-19 vaccinations. For this study, no additional visits or invasive procedures will be performed in addition to standard care.

**Results:**

As of August 2024, the study has enrolled 32 patients. The recruitment phase is still ongoing.

**Conclusions:**

Results will be used to optimize vaccination and booster schedules for patients who are immunocompromised and to increase rates of protection against severe SARS-CoV-2 infections. Further, results may identify risk and treatment factors, which lead to low immune responses in patients vaccinated against COVID-19, as well as the impact of repeated vaccination on B- and T-cell responses.

**Trial Registration:**

ClinicalTrials.gov NCT05597761; https://clinicaltrials.gov/study/NCT05597761

**International Registered Report Identifier (IRRID):**

DERR1-10.2196/60675

## Introduction

The novel SARS-CoV-2 was identified in December 2019 as a cause of severe pneumonia, acute respiratory distress syndrome, and potential multiorgan failure in humans [1,2]. The disease known as COVID-19 has turned into a worldwide pandemic, causing substantial morbidity and mortality, and is now (2024) considered an endemic disease. As of December 15, 2024, the World Health Organization reports a total of 7,079,587 COVID-19 deaths worldwide [3]. Patients who are immunocompromised, such as those with hematological malignancies, are highly affected by SARS-CoV-2 infections due to the high risk of severe courses of infection [4-8]. COVID-19 may not only result in a delay or discontinuation of the treatment for the underlying diseases but also result in high mortality rates of above 30% [4-6,9,10]. Prevention strategies are therefore focused on avoiding SARS-CoV-2 infection in these vulnerable patients and reducing the risk of critical disease following infection. This is addressed by nonpharmacological and pharmacological interventions. Nonpharmacological interventions such as wearing masks, physical distancing, and respiratory hygiene are effective for reducing SARS-CoV-2 transmission but were withdrawn for the general population by state authorities as of June 2022. For example, masking in public is no longer mandatory in many countries. Pharmacological interventions included several antiviral drugs as well as various therapeutic monoclonal antibodies that lost neutralizing capacity with the emergence of Omicron variants [11,12]. At the end of 2020 and the beginning of 2021, the first messenger RNA vaccines against COVID-19 were proven to be effective in the prevention of severe SARS-CoV-2 infection and licensed for use [13-15]. The German Standing Committee on Vaccination of the Robert Koch Institute (RKI) has been recommending 3 antigen contacts (infection or vaccination) to complete basic immunization, of which at least one should be by vaccination. Annual booster recommendations are advised for groups at high risk, such as people with an impaired immune response [16]. COVID-19 vaccination, therefore, represents the mainstay of COVID-19 prevention. Efficacy and safety have been demonstrated for several vaccines, leading to currently 15 vaccines listed by the Paul Ehrlich Institute in Germany and with marketing authorization in Europe (as of October 2024) [17]. Studies have shown that COVID-19 vaccination is efficient in patients who are immunocompromised. However, lower levels of antibodies have been reported in this patient group [18,19]. Patients who are immunocompromised had been excluded from the majority of registered studies. Further, studies focused mainly on B-cell immune responses, resulting in uncertainty regarding the extent of immune response and the role of T cell–generated immune response in these patients. The aim of this study is to determine the immunogenicity and reactogenicity of an implemented standard-of-care (SOC) COVID-19 vaccination strategy (Multimedia Appendix 1) in patients who are immunocompromised [20].

## Methods

### Overview

A new SOC vaccination strategy was implemented for patients who are immunocompromised at 3 university hospitals in Germany, the University Hospital of Aachen, Cologne, and Essen. This approach targets a vaccination strategy that is guided by individual immune responses to COVID-19 vaccines [20] (Multimedia Appendix 1).

### Study Design

This is a multicenter, prospective, noninterventional study conducted at university hospitals in Germany that have implemented the SOC COVID-19 vaccination for patients who are immunocompromised [20]. This study aims to analyze the humoral and cellular immune response data generated within the procedures of the SOC COVID-19 vaccination [20]. Patients who are immunocompromised and will be vaccinated according to the vaccination standard [20] are eligible for study inclusion. To define immunocompromised, the classification “Stages of Immunosuppression” [21] was considered (Multimedia Appendix 2). Patients in stage 3 (eg, patients with a hemato-oncological underlying disease or patients receiving biologicals) are eligible for study inclusion. At each vaccination visit and follow-up visit, both defined in the vaccination standard, enrolled patients will undergo study-related assessment in addition to routinely performed assessments and interventions within their standard care. At the first visit, a SARS-CoV-2 antigen test will be performed. In case of a positive test result, the patient will be excluded from study enrollment. According to the vaccination standard [20], blood draws will be performed at each visit. For study purposes, additional blood samples will be drawn by using the same vein puncture at these visits (see visits and study-related assessments). These samples will be used for additional analysis of the immune response. The samples will be collected and stored until the analysis, which will be performed after the recruitment period. This guarantees that results obtained from study-related immune response assessments do not affect the standard vaccination strategy. Patients will also receive a patient diary before the first vaccination to document adverse drug reactions (ADRs) to the COVID-19 vaccine.

### Study-Related Tests

Peripheral blood mononuclear cells will be isolated from whole blood ethylenediaminetetraacetic acid–containing tubes using density-based separation with Ficoll. Cells will be cryopreserved for immune phenotyping by flow cytometry at the end of the study. Immune phenotyping of lymphocytes allows specific analyses of lymphocytic subsets, which are defined by a higher number and composition of surface antigens. Using a customized panel of antibodies, we will be able to detect the major subsets of B- and T-cell lymphocyte lineages. All study-related immune response measurements will be performed in batches from stored samples after last-patient-last-visit at the University Hospital of Cologne. Sample remains are disposed of after study completion.

### Objectives

Data for primary and secondary objectives are generated within the routine procedures of SOC COVID-19 vaccination [20]. Data for exploratory objectives will be generated from study-related assessments based on study-related blood sampling. Study-related blood sampling will be performed at the same timepoints and from the same vein puncture as for routine standard procedures (Textbox 1).

Primary, secondary, and explorative objectives.
**Primary objective**
To analyze the available data on anti-spike–immunoglobulin G titers after repeated messenger RNA (mRNA) vaccinations in immunocompromised patients
**Secondary objectives**
To analyze the available data on neutralizing capacity against the Omicron-BA.1 variant after repeated mRNA vaccinations in immunocompromised patientsTo analyze the available data on neutralizing capacity against other Omicron sublineages after repeated mRNA vaccinations in immunocompromised patientsTo analyze the available data on binding antibody response against Omicron variants after repeated mRNA vaccinations in immunocompromised patientsTo analyze the available data on the waning of the humoral immune response against Omicron variants after the last mRNA vaccination in successfully vaccinated patients according to the standard of careTo analyze reactogenicity data (see solicited adverse events) collected within this study
**Explorative objectives**
To evaluate B- and T-cell immune response against Omicron variants after repeated mRNA vaccinations in immunocompromised patientsTo evaluate the waning of B- and T-cell immune response against SARS-CoV-2 (in particular Omicron variants) after the last mRNA vaccination in successfully vaccinated patients according to the standard of careTo evaluate memory B-cell response against the Omicron variant after the last mRNA vaccine, in successfully vaccinated patients

### End Points

The end points are listed in Textbox 2.

Primary, secondary, and exploratory endpoints.
**Primary end point**
Time to reach an adequate immune response according to the recent version of the COVID-19 vaccination standard-of-care [20] after repeated messenger RNA (mRNA) vaccinations (Multimedia Appendices 1 and 3)
**Secondary end points**
Time to Omicron BA.1-specific neutralizing antibody ID_50_ (50% inhibitory dilution) titers ≥30 after repeated mRNA vaccinations in immunocompromised patientsTime to anti-spike-1/2 IgG (immunoglobulin G) increase ≥33.8 binding antibody units (BAU)/mL measured by SARS-CoV-2 TrimericS IgG (DiaSorin) after repeated mRNA vaccinations in immunocompromised patientsTime to decrease of Omicron BA.1–specific neutralizing antibody ID_50_ titers <30 after last mRNA vaccination in successfully vaccinated patients according to the standard-of-careTime to anti-spike-1/2 IgG decrease <33.8 BAU/mL after the last mRNA vaccination in successfully vaccinated patients according to the standard-of-care measured by SARS-CoV-2 TrimericS IgGAnti-spike-1/2 IgG titer ≥ 33.8 BAU/mL was interpreted as reactive, according to the manufacturer’s instructions (DiaSorin). To determine Omicron BA.1-specific neutralizing serum titers, the lowest tested serum dilution was 1:30, which served as the lower limit of quantification.
**Exploratory end points**
Time to detection of SARS-CoV-2–specific T-cell immunityTime to detection of SARS-CoV-2–specific antibody-secreting plasma cellsTime to detection of SARS-CoV-2–specific memory B cellsTime to waning of SARS-CoV-2–specific T cellular immunityTime to waning of SARS-CoV-2–specific antibody-secreting plasma cellsTime to waning of SARS-CoV-2–specific memory B cells

### Study Cohort

Eligibility criteria and other details have been listed in Textbox 3.

Eligibility criteria, premature study withdrawal, and enrollment failure
**Inclusion criteria**
Patient is vaccinated according to the recent version of the COVID-19 vaccination standard for immunocompromised patients [20]Patient is 18 years of age or older at enrollmentWritten informed consent from patient has been obtained prior to any study-related procedures (see obtaining informed consent)Patient is immunocompromised according to stage 3 classification “Stages of Immunosuppression” [21] (Multimedia Appendix 2)
**Exclusion criteria**
Patient is not vaccinated according to the recent version of the COVID-19 vaccination standard [20]Patient has a positive SARS-CoV-2 antigen test at the first visit
**Premature withdrawal from the study**
In case a patient fulfills one of the following criteria, the patient must be withdrawn from the studyPatient has reached an adequate immune response as defined in the recent version of the COVID-19 vaccination standard [20] at the first visitIn case a patient has to withdraw prematurely from the study, all data that have been collected between enrollment and withdrawal will be used for the analysis.

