**Visit 1**
Following assessments will be performed at this visit:Review of inclusion and exclusion criteriaWritten informed consent will be obtainedDemographics including age and sex will be obtainedRelevant medical history including all prior chemotherapy regimens and radiation therapy will be collectedCollection and review of previous and concomitant medicationSARS-CoV-2 antigen test obtained from nasal, pharyngeal, nasopharyngeal, or oropharyngeal swabPatient diary will be handed out and explained to the patient. Patient is instructed to record solicited adverse events that occur within 7 days after the time of vaccination in the patient diary (the day of vaccination plus the following 6 days)Prevaccination blood sampling for SARS-CoV-2–specific B- and T-cell immune response assessment will be performed (maximum 36 mL blood)

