**Follow-up visit 1**
The following assessments will be performed at this visit:Collection of patient diary and documentation of adverse events (see Safety section for details). The patient diary will remain at the study site together with the patients’ medical recordsBlood sampling for SARS-CoV-2–specific B- and T-cell immune response assessment (maximal 18 mL blood)

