**All following follow-up visits**
The following assessment will be performed at all subsequent follow-up visit:Blood sampling for SARS-CoV-2–specific B- and T-cell immune response assessment (maximal 18 mL blood)Previous and concomitant medication of interestInformation on previous and concomitant immunosuppressive medication within 90 days prior to providing informed consent will be recorded in the electronic case report form. In addition, all COVID-19 vaccinations and all therapeutic neutralizing antibodies against SARS-CoV-2 (tixagevimab-cilgavimab, sotrovimab, convalescent plasma, etc) a patient has ever received will be documented in the electronic case report form.

**Table 1 table1:** Visit schedule.

Procedures	Vaccination period		Follow-up period	
	Visit 1	All following visits^a^	FU^b^ 1	All following FUs
Day^c^	0^c^ (42^d^)	28-day intervals^c,d^	28^e^	28-day intervals^e^
Visit window (days)	±5	±5	±5	±5
Informed consent	✓			
Demographics	✓			
Review of inclusion and exclusion criteria	✓			
Medical history	✓			
Concomitant medication	✓	✓	✓	✓
SARS-CoV-2 antigen test	✓			
SARS-CoV-2–specific B- and T-cell immune response^f^	✓	✓	✓	✓
Dispensing of the study diary	✓			
Collection of the study diary			✓	
Review of diary and documentation of solicited adverse events^g^		✓	✓	
Complete case report form	✓	✓	✓	✓
Standard cellular immunity^h,i^	✓	✓	✓	✓
SARS-CoV-2 Quantiferon^i^	✓	✓	✓	✓
Omicron-BA.1–specific nAB^i,j,k^	✓	✓	✓	✓
Anti-spike-1/2 IgG^l^ antibodies^i,j^	✓	✓	✓	✓
Anti-nucleocapsid IgG^l^ antibodies^i^	✓	✓	✓	✓
Anti-SARS-CoV-2 vaccination^i^	✓	✓		

^a^Visit only in case anti-spike-1/2-IgG titer was <847 BAU (binding antibody units)/mL at the previous visit according to standard-of-care COVID-19 vaccination.

^b^FU: follow-up.

^c^Day 0 is the day of the first visit and first vaccination. All days in the vaccination phase are counted in relation to the last vaccination, respectively.

^d^Applicable for patients posthematopoietic stem cell transplantation (HSCT) or chimeric antigen receptor (CAR)–T cell treatment. Day 0 is considered the day of HSCT or CAR-T cell treatment. All days in the vaccination phase are counted in relation to the day of HSCT or CAR-T cell treatment, respectively.

^e^Days in the follow-up phase are always counted in relation to the last vaccination.

^f^Maximum 36 mL blood is collected at visit 1. At all other visits, maximum 18 mL blood is collected.

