### Safety

#### Solicited Adverse Events

In order to evaluate the reactogenicity of COVID-19 vaccinations applied within the SOC [20], this study collects solicited adverse events (AEs) for 7 days (the day of vaccination plus the following 6 days) after each vaccination. As a noninterventional study, this study focuses on solicited AEs only, that is, on a subset of all AEs. Solicited AEs will be collected by the patient using a patient diary. Solicited AEs will be documented starting on the day of each vaccination within the SOC [20] and the following 6 days. The grading system of solicited AEs is based on the Toxicity Grading Scale for Healthy Adult and Adolescent Volunteers Enrolled in Preventive Vaccine Clinical Trials [22] and the Common Terminology Criteria for Adverse Events v5.0 (CTCAE) [23] grading systems (Multimedia Appendix 2).

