### Statistical Considerations

The primary analysis set comprises all enrolled patients who received at least one vaccination within the COVID-19 vaccination standard [20]. The statistical analysis is essentially descriptive and focuses on estimation of the time to event, that is, primary and secondary end points. The event-time distributions are described by the Kaplan-Meier method [24] with pointwise 95% confidence bounds [25] (18, “log-log”). Relevant percentiles (eg, quartiles) with 95% CIs are derived. Generally, quantitative variables are summarized by mean, SD, and percentiles (0, 25, 50, 75, 100), and qualitative variables by absolute (ie, count) and relative (ie, percentage) frequencies. Extreme values (“outliers”) are flagged and listed.

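### A patient dosed at visit 1 and then withdrawn for an already adequate response has no scheduled visit at which the reaction diary is reviewed or collected

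*Protocol article*

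**What the plan says.** - **Dose at visit 1.** Table 1 ticks vaccination at visit 1 without condition, and footnote c states: "Day 0 is the day of the first visit and first vaccination". Only the later vaccination visits depend on a titer. Footnote a reads "Visit only in case anti-spike-1/2-IgG titer was <847 BAU" per mL at the previous visit.
- **Titer and diary at visit 1.** Routine anti-spike antibodies are measured at visit 1 (Table 1), and the study blood sample is taken before the dose (Textbox 4). The diary is handed out at the same visit: "Patient is instructed to record solicited adverse events that occur within 7 days after the time of vaccination in the patient diary".
- **Withdrawal.** Textbox 3 lists one criterion for mandatory withdrawal, an adequate response already present at the first visit. It adds that "all data that have been collected between enrollment and withdrawal will be used for the analysis".
- **Diary return.** In Textbox 4 and Table 1 the diary is reviewed at later vaccination visits and at follow-up visit 1. It is collected only at follow-up visit 1, scheduled 28 days after the last vaccination.
- **Promise.** Under Solicited Adverse Events: "this study collects solicited adverse events (AEs) for 7 days (the day of vaccination plus the following 6 days) after each vaccination".
- **Analysis set.** Statistical Considerations puts every enrolled patient with at least one vaccination under the standard into the primary analysis set.

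**The concern.** Each rule is reasonable alone, but together they leave a gap. A patient can receive a dose that the study undertakes to follow for 7 days, and then be removed by the study's own rule before any visit at which the diary would be seen.

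Reactogenicity is a secondary objective. The missing diaries would not be a random subset, because the rule selects on baseline antibody response. First-dose reaction rates would come only from patients below the adequate threshold, while the stated aim covers immunocompromised patients vaccinated under the standard. The withdrawn patients would still be in the primary analysis set, so a reader could take the rates to describe everyone who was dosed.

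**Working it through.** The plan gives no figure for this point. Table 3 concerns the precision of the time-to-event estimates and is not affected. The check is a walk through the schedule.

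**1. Path of a patient whose visit 1 response is adequate**

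| Step | Rule | Diary contact |
|---|---|---|
| Visit 1: blood drawn, dose given, diary handed out | Table 1, footnote c; Textbox 4 | Dispensed only |
| Visit 1 response found adequate: withdrawal required | Textbox 3 | None described |
| Next vaccination visit | Table 1, footnote a: only if the titer was below 847 BAU/mL | Does not take place |
| Follow-up visit 1, day 28 after the last dose | Study assessment, but the patient has been withdrawn | Does not take place within the study |

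Scheduled contacts with diary review or collection after the dose: 0. Reading adequate as at or above 847 BAU/mL is an inference from footnote a, since the definition is in appendices not shown. The path does not depend on that reading, because withdrawal alone ends the study visits.

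**2. Does the timing of the titer result change this?** The article gives no turnaround time.

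- Result known before the dose, and no dose given: no reactogenicity is lost. But Table 1 and footnote c then lack a condition, and they conflict with the withdrawal rule as it operates.
- Result known after the dose but within the 7 days: the diary is incomplete at withdrawal, and no contact is scheduled to obtain it.
- Result known after the 7 days: the diary may be complete, but it is with the patient and no handover is scheduled.

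Either diary data have no scheduled route to the site, or two parts of the article disagree.

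**3. Form of the bias.** Let w be the share of dosed patients withdrawn this way, p_R the first-dose reaction rate in retained patients and p_W the rate in withdrawn patients. The rate in all dosed patients is (1 − w)p_R + w·p_W. If only retained patients are observed, the estimate is p_R, so

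bias = p_R − [(1 − w)p_R + w·p_W] = w(p_R − p_W).

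The documents give neither w nor the difference. Both are assumed here, with 100 dosed patients. Half-width = 1.96 × √(0.25/n) at a rate of 50%, compared with 9.8 points for n = 100.

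| Assumed w | Patients with first-dose diary, n | Half-width (points) | Bias, 10-point difference | Bias, 20-point difference | Bias, 30-point difference |
|---|---|---|---|---|---|
| 5% | 95 | 10.1 | 0.5 | 1.0 | 1.5 |
| 10% | 90 | 10.3 | 1.0 | 2.0 | 3.0 |
| 20% | 80 | 11.0 | 2.0 | 4.0 | 6.0 |
| 30% | 70 | 11.7 | 3.0 | 6.0 | 9.0 |
| 40% | 60 | 12.7 | 4.0 | 8.0 | 12.0 |

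Example: w = 0.20 with a 20-point difference gives 0.20 × 20 = 4.0 points. If the two groups react alike, the bias is zero and only precision is lost.

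**The case against.** The best reply is that the premise is unproven. The strategy is guided by individual immune response, the standard itself is not shown, and limiting the analysis set to patients with at least one dose leaves room for enrolled patients who had none. Those already adequate at visit 1 could be such patients. This stands as a condition on the point. It does not remove the point, because the visit schedule as printed gives the dose to everyone at visit 1.

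A second reply is that a condensed article need not describe diary return after early exit, that the vaccination and follow-up visits belong to routine care and may continue, and that the text on withdrawal says which data will be used without forbidding retrieval of the diary. This is also fair, so the gap can be claimed only for the schedule as published. But the article itself prints the withdrawal rule, the diary procedure and the promise of collection after each dose, and these do not fit together. The paragraph on enrollment failure asks for adverse events up to withdrawal, but for a different category of patient, and the 7 days may not be over by then.

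A reader might infer three stronger things that the documents do not support:

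- **Diluted reaction rates.** This needs missing diaries to be counted as no reaction. The article states no such rule and sets no denominator for reactogenicity.
- **Unrecorded serious events.** The Adverse Drug Reactions section separately requires serious events within 7 days of each vaccination to be entered in the eCRF, without tying this to the diary. One can say only that no contact is scheduled to obtain them for these patients.
- **A special defect for all early leavers.** Losing the last diary when a patient drops out is common to diary studies. The specific issue here is the loss created by the study's own withdrawal rule.

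**Conclusion.** The point holds in limited form. Under the published rules, a patient dosed at visit 1 and withdrawn because the response was already adequate has no scheduled visit at which the diary is reviewed or collected. This conflicts with the promise of 7-day solicited adverse events after each vaccination. The loss falls on a group selected by baseline response, so first-dose reactogenicity would describe only patients below the adequate threshold.

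This rests on the dose being given before the titer is acted on, as Table 1 implies, and on there being no diary-return route outside the visits. If the first does not hold, Table 1 and the withdrawal rule must be reconciled instead. The size of the bias cannot be established from the documents, and the tabulated values only show how it scales. A secondary objective is affected, not the precision of the primary end point. The correction is worth making because it is specific and cheap.

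**What to change.** Amend the withdrawal paragraph in Textbox 3 so that withdrawal for an adequate response at visit 1 ends immune sampling, but not the 7-day diary and serious adverse event collection for a dose already received. Let the diary be returned by post or at a routine appointment and entered in the eCRF. State when the visit 1 titer becomes available relative to the dose, and make Table 1, footnote c and the withdrawal rule agree.

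Report solicited adverse events per dose among patients with diary data, with the number of doses lacking a diary and the reason. For patients already enrolled (32 as of August 2024, with recruitment open), count those withdrawn under this rule and retrieve their diaries where possible.

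The cost is a short amendment, a return envelope or a reminder call, and slightly more site follow-up. Any new patient-facing document has to go to the ethics committee before use. No extra visit or blood draw is needed.
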